**Fig 2 pone.0306422.g002:**
[figure not shown]
Course of study overview.

### 2.2 Ethics committee and regulatory approval

The trial will be conducted in accordance with the ethical principles outlined in the Declaration of Helsinki 2013. This research has received approval from the Research Ethics Committees of Iran University of Medical Sciences under Approval ID: IR.IUMS.REC.1401.02 and prospectively registered with clinicaltrials.gov under the identifier NCT05200962. In the event of any severe side effects occurring during the trial, they will be promptly reported to the safety monitoring board and the Institutional Review Board (IRB) for appropriate management.

### 2.3 Participants and recruitment

We aim to recruit 48 participants from specialized clinics affiliated with Razi Psychiatric Hospital in Shahre-Rey, Iran, using flyer advertising and referrals from their treating psychiatrists. The exclusion of smokers is not feasible because a significant proportion of patients with SCZ are smokers. The expected population is SCZ patients with cognitive impairment (see inclusion criteria) who are not in a severe stage. Below are the inclusion and exclusion criteria:

Inclusion Criteria:

To be eligible for participation, individuals must meet the following criteria

Age: Men or women aged 18–55 years.Diagnosis of schizophrenia or schizoaffective disorder according to DSM-5 with the native language version of the DSM-5 Clinician-Rated Dimensions of Psychosis Symptom Severity [33] and the native language version of the Positive and Negative Syndrome Scale [31] conducted by two skilled licensed psychiatrists. Patients with disorganized or negative motor behaviors will not be included.Cognitive Impairment: Should exhibit significant cognitive impairment, defined as performance of at least one standard deviation below the norm on working memory/executive functioning tasks measured by a native language version [27] of the Montreal Cognitive Assessment [34].Feasibility: Must be suitable for tDCS interventions following safety guidelines.Treatment with stable doses of antipsychotics and all CNS-activating medications (4–6 weeks before the experiment). For the purpose of this study, stability is defined as a change of not more than 50% in the antipsychotic dose.Right-HandednessInformed Consent: Written and witnessed informed consent (the informed consent is provided by independent research assistants and not the treating psychiatrist to avoid coercive treatment)Participants must read and write in Persian at a level sufficient to understand and complete study-related procedures

Exclusion Criteria:

Participants will be excluded from the study if they meet any of the following criteria.

PregnancySubstance DependencePresence of other neuropsychiatric disorders except for schizoaffective disordersSeizure HistoryNeurological DisorderHead InjuryThe presence of ferromagnetic objects in the body that are contraindicated for MRI of the head (pacemakers or other implanted electrical devices, brain stimulators, some types of dental implants, aneurysm clips, metallic prostheses, permanent eyeliners, implanted delivery pumps, or shrapnel fragments), or fear of enclosed spaces).

### 2.4 Plans to promote participant retention

To enhance participant engagement and alleviate anxiety, a video explaining the project’s execution process, including details about the MRI environment and sounds, is presented by a qualified psychiatrist one week before the intervention. This video includes a mock model of a 3 Tesla scanner (Siemens Prisma) to familiarize participants with the MRI atmosphere. They are encouraged to ask questions and express concerns. On the testing day, a team of trained researchers welcome the participants and they remained with them throughout the experiment. Any adverse effects are diligently recorded, and participants are provided with contact information of the research team psychiatrist in case of post-study side effects. Participants are informed of their right to withdraw from the study at any time, with the assurance that their data will be excluded from the final results if they choose to do so.

### 2.5 Sample size estimation

The sample size is determined a priori through power analyses via G*Power 3.1 [35], indicating that a minimum of 42 subjects is required to achieve 95% power at a significance level of 0.05 for the primary statistical test of a mixed-model ANOVA design, with two groups, 3 measurements of working memory performance (baseline, during stimulation and 24 hours after stimulation), given a medium effect size (f = 0.25, equivalent to η^p2^ = 0.10 which is used in ANOVA models). This effect size is recommended in NIBS studies [36]. To account for a potential dropout rate during the study, we propose including an additional 3 participants in each group (i.e., 6), totaling 48, which is more than the majority of published studies in terms of sample size and retention rate [37, 38].

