**Methods:**

The study is designed as a randomized, double-blind, 2-arm parallel-group, sham-controlled, trial. Forty-eight participants with SCZ and cognitive impairment (measured via a set of executive functions tests) will be randomly allocated to receive either a single session of active (n = 24) or sham (n = 24) tDCS (20-min, 3-mA). The anodal and cathodal electrodes are positioned over the left and right DLPFC respectively. The stimulation occurs concurrently with the working memory task, which is initiated precisely 5 minutes after the onset of tDCS. Structural and resting-state (rs-fMRI) scans are conducted immediately before and after both active and sham tDCS using a 3 Tesla scanner (Siemens Prisma model) equipped with a 64-channel head coil. The primary outcome will be changes in brain activation (measures vis BOLD response) and working memory performance (accuracy, reaction time).

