### 2.10 Outcome measures and assessments

#### 2.10.1 Working memory task

To assess working memory performance, we will employ the N-back task, a widely recognized ’executive’ assessment for working memory (WM) (Fig 3) related to the prefrontal cortex (PFC) [41]. This task requires continuous monitoring and updating of the remembered information. Participants will be presented with a sequence of numbers one at a time and are instructed to indicate when the current number matches the one presented n” steps earlier in the sequence. The working memory demand increases with higher ’n-back’ levels. In our study, participants will engage in both 1-back and 3-back conditions in line with previous works [42], once prior to the intervention (tDCS/fMRI) session for baseline assessment and once during the online stimulation. In the 1-back task, participants identify when the current number stimulus matched the one immediately preceding it, placing minimal demand on the working memory. In the more challenging 3-back, participants must recognize when the current stimulus matches the one shown three steps back, necessitating the maintenance and manipulation of information in working memory.

The N-back test will be implemented using MATLAB (MathWorks, Inc., 2019) and the PsychToolbox library. The experiment comprised 120 trials, with each stimulus (a digit between 0–9) displayed for 0.5 seconds followed by an inter-trial interval (ITI) that was dependent on the N-back level, calculated as 2 + 0.25 * (N_back_-1) seconds. Participants were prompted to respond by pressing the ’Space’ key for N-back instances. During the training stage, a shorter version with visual feedback will be applied, where the screen turns red when the wrong button is pressed, and green for the correct response. Outcome measures include accuracy, reaction time for correct responses (ms), and d-prime—a bias-free measure of observer sensitivity [43] considering both correct hits and false alarms. D-prime is calculated as

d′=z(Hitrate)−z(Falsealarmrate)

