### 2.12 Statistical methods

To assess the efficacy of the tDCS intervention, we will conduct a mixed model analysis of variance (mixed-ANOVA) on the n-back task indices, including d-prime, reaction time, and accuracy with time (before and after tDCS) as the within-subject factor and group (active tDCS and sham tDCS) as the between-group factor and their interaction. The group × time interaction effect and the main effect of group and time will be explored to see if changes in working memory performance and brain activation (two key dependent variables) are influenced by the type of stimulation (group factor) and time (before vs during stimulation). The normality and homogeneity of data distribution, and variance will be confirmed by Shapiro-Wilk and Levin tests, respectively. Mauchly’s test will also be used to evaluate the sphericity of the data before performing the ANOVA. In case the assumption of sphericity was violated, the degrees of freedom were corrected using Greenhouse-Geisser estimates of sphericity. To investigate the associations between changes in brain activity/connectivity and task performance changes, we will employ the Pearson correlation test. This test will help identify potential relationships between changes in brain activity and task performance, providing valuable insights into the neural mechanisms underlying our observations. All statistical analyses will be conducted using R [45].

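### The sample size is built on three n-back occasions, but the task and analysis sections describe two, so the stated 95% power belongs to a different test and no analysis of the 24-hour primary component is stated

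*Protocol article*

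**What the plan says.** The protocol article describes the n-back occasions in four places.

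- **Section 2.5 (sample size)** counts three: "3 measurements of working memory performance (baseline, during stimulation and 24 hours after stimulation". The power calculation is "for the primary statistical test of a mixed-model ANOVA design, with two groups", and it concludes that "a minimum of 42 subjects is required to achieve 95% power at a significance level of 0.05", "given a medium effect size (f = 0.25, equivalent to" a partial eta-squared of 0.10). Six are added for dropout: "we propose including an additional 3 participants in each group (i.e., 6), totaling 48".
- **Section 2.10.2 (primary outcomes)** also counts three. Changes in d-prime, accuracy and reaction time are each defined from baseline to the online session and at 24 hours.
- **Section 2.10.1 (task)** counts two. The 1-back and 3-back conditions are done "once prior to the intervention (tDCS/fMRI) session for baseline assessment and once during the online stimulation". No 24-hour administration is listed, and the visit description in section 2.1 mentions none.
- **Section 2.12 (analysis)** also counts two. The mixed ANOVA is run "with time (before and after tDCS) as the within-subject factor and group (active tDCS and sham tDCS) as the between-group factor". The next sentence describes the same factor as before versus during stimulation. The section then plans Mauchly's test and a Greenhouse-Geisser correction.

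**The concern.** These four statements cannot all hold. If 2.10.1 is followed, the 24-hour part of three primary outcomes is not collected. If 2.12 is followed, it has no stated analysis even if it is collected. In either case the test described in 2.12 is not the one for which 42 participants and 95% power were derived.

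Two things are at stake. One is the power statement, which a reader will take as describing the planned analysis. The other is the definition of the primary analysis: the single post-baseline level carries two labels (after and during), and a third time point is primary in one section and absent from another. Objective 1 in the Introduction concerns performance during stimulation, so the online comparison should be identifiable without inference.

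**Working it through.** **Inputs.** From section 2.5: two groups, three measurements, f = 0.25, alpha 0.05, 42 completers, 48 enrolled. From the Abstract: equal arms, "a single session of active (n = 24) or sham (n = 24) tDCS". From section 2.12: two levels of time. The document gives neither the correlation among repeated measurements (rho) nor a sphericity value. I assume rho = 0.5 and full sphericity, and vary rho below.

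**Formula.** For the group-by-time interaction with two groups and m measurements, power comes from the noncentral F distribution with

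- lambda = f² × N × m / (1 − rho)
- df1 = m − 1
- df2 = (N − 2)(m − 1)

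**Step 1: reproduce the plan's figure (m = 3).** At N = 42, lambda = 0.0625 × 42 × 3 / 0.5 = 15.75 with df 2 and 80, so power is 94.6%. The first N to reach 95% is 43, or 44 with equal arms. This agrees with the stated 42 and 95% to within rounding; rho of about 0.51 to 0.53 gives 42 exactly. The stated figure is therefore consistent with a three-occasion interaction test at f = 0.25.

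**Step 2: the two-level test of section 2.12 (m = 2), with f and rho unchanged.**

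| N | lambda | df | Power |
|---|---|---|---|
| 42 | 0.0625 × 42 × 2 / 0.5 = 10.5 | 1, 40 | 88.5% |
| 48 | 0.0625 × 48 × 2 / 0.5 = 12.0 | 1, 46 | 92.4% |
| 54 | 0.0625 × 54 × 2 / 0.5 = 13.5 | 1, 52 | 95.0% |

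**Step 3: vary the unstated correlation (m = 2, f = 0.25).**

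| rho | Power at N = 42 | Power at N = 48 |
|---|---|---|
| 0.3 | 76.2% | 81.8% |
| 0.5 | 88.5% | 92.4% |
| 0.55 | not computed | 94.7% |
| 0.6 | not computed | 96.6% |
| 0.7 | 98.3% | not computed |

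At N = 48 the two-level test reaches 95% from rho of about 0.56.

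**Step 4: hold the arm differences constant instead of f.** f² is proportional to the variance of the arm differences across the occasions included, so it changes when an occasion is dropped. Write the differences at baseline, online and 24 hours as a pattern in d. For the two occasions (0, d) the variance is d²/4.

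- Patterns (0, d, d) and (0, d, 0): the three-level variance is 2d²/9. The ratio is (1/4)/(2/9) = 1.125, so f² becomes 0.0625 × 1.125 = 0.0703 and f is about 0.265. At rho = 0.5, power is 91.8% at N = 42 and 94.9% at N = 48.
- Pattern (0, d, d/2), an effect that half-fades: the three-level variance is d²/6. The ratio is (1/4)/(1/6) = 1.5, so lambda at N = 42 is 10.5 × 1.5 = 15.75. That is the three-level value, now on 1 df, and power is 97.2%.

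**Step 5: the sphericity text.** With two levels there is only one difference between occasions, so sphericity cannot be violated. Mauchly's test and the Greenhouse-Geisser correction have a function only from three levels upward.

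**The case against.** The strongest reply is that a three-level ANOVA was intended all along. Sections 2.5 and 2.10.2 both include 24 hours, the sphericity procedures in 2.12 make sense only with three levels, and the two-level descriptions in 2.10.1 and 2.12 would then be loose wording. The SPIRIT schedule and course-of-study figures are not shown and may list a 24-hour visit, and a separate analysis plan may exist. Part of this stands. A reader might infer that the 24-hour outcome is never tested, and the documents do not support that: they show only that this article states no analysis for it. The conflict remains, because 2.12 describes two levels twice and 2.10.1 lists two administrations. A figure showing a 24-hour visit would not change either statement.

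A second reply concerns the power. A reader might infer that the type II error at 42 completers is 11.5% rather than 5%. That holds only if f stays at 0.25 and rho is 0.5. Steps 3 and 4 show that the two-level test can fall well short of the target or exceed it. This objection stands in full.

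A reader might also infer that the headline comparison is open to choice once the data are seen. The documents do not go that far. Objective 1, section 2.10.1, each n-back outcome in 2.10.2 and one of the two labels in 2.12 all point to baseline versus online, and nothing offers 24 hours as a substitute. The opening is limited to the loose label of before and after stimulation.

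Finally, a three-level omnibus test followed by contrasts is a legitimate design, and follow-up contrasts are often left to the analysis plan. Making the 1-df contrast the sole primary test is therefore a preference and not a correction.

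**Conclusion.** The inconsistency is established without any assumption: two sections use three n-back occasions, two use two, and section 2.12 is inconsistent with itself. It follows that the 95% power belongs to a different test from the one described in 2.12, and that the 24-hour component of three primary outcomes has no stated analysis here and no listed administration in 2.10.1.

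The size of any power loss is conditional. With f = 0.25, rho = 0.5 and sphericity, the two-level test loses about 6 percentage points at 42 completers (94.6% to 88.5%) and stands 2.6 points below the 95% target at 48 (92.4%). Other plausible values of rho, or constant arm differences in place of constant f, widen this loss, remove it or reverse it. The documents do not show that the trial is underpowered. The point still needs correcting, because it concerns the definition of a primary analysis and the figure that justifies the sample size.

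**What to change.** Make the number and timing of n-back occasions identical in sections 2.1, 2.5, 2.10.1, 2.10.2 and 2.12, in one of two ways:

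- **Keep the 24-hour test:** list it in 2.10.1 and the visit description, and give time three levels in 2.12. The sphericity text then has a purpose.
- **Drop it:** remove it from 2.5 and 2.10.2, and delete the sphericity text from 2.12.

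In both cases, use one label for the online measurement and state that the between-arm change from baseline to the online session is the comparison that answers objective 1. Restate the power for the test actually used, giving its assumed correlation and effect size. Under the current f and a correlation of 0.5, a two-level test would read about 88.5% at 42 completers and 92.4% at 48.

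The cost is protocol and analysis-plan wording and possibly a less favourable stated power. No extra participants are needed. Section 2.1 says recruitment is under way, so the change should be made and dated before unblinding.

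### Section 2.5 equates f = 0.25 with partial eta-squared 0.10, which is wrong, and labels as medium what its own calculation treats as an arm difference of about 1.06 single-visit SD

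*Protocol article*

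**What the plan says.** Section 2.5 states that "The sample size is determined a priori through power analyses via G*Power 3.1" and that "a minimum of 42 subjects is required to achieve 95% power at a significance level of 0.05". The test is a mixed-model ANOVA "with two groups, 3 measurements of working memory performance (baseline, during stimulation and 24 hours after stimulation". The planning effect is introduced as "given a medium effect size (f = 0.25, equivalent to η^p2^ = 0.10 which is used in ANOVA models", with the remark that "This effect size is recommended in NIBS studies". The 42 is raised for dropout by "including an additional 3 participants in each group (i.e., 6), totaling 48", which agrees with the 24 per arm in the abstract.

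The article gives no expected arm difference or SD for any n-back measure, no correlation among the three measurements, and no indication of which G*Power effect-size option was used.

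**The concern.** Cohen's f and partial eta-squared are tied by a fixed formula, and the printed pair does not satisfy it. The sentence therefore contains two different planning effects, and the sample size can belong to only one of them. Because 0.10 is presented as the ANOVA-scale figure, a reader will take it as the effect the trial has 95% power to find.

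The word medium adds to the problem. It is the usual label for f = 0.25 in a one-way between-group ANOVA, where two groups then differ by 0.5 SD. In a repeated-measures interaction the same f can stand for a much larger difference. If so, a null result could be read as excluding effects that the trial would probably miss. That matters because the Discussion offers the data as support for larger trials.

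**Working it through.** **Inputs.** From section 2.5: k = 2 groups, m = 3 measurements, f = 0.25, alpha 0.05, power 0.95, N = 42, enlarged to 48. From section 2.12: the group × time interaction, taken as the effect of interest. Assumed because not stated: correlation ρ = 0.5 among measurements, and sphericity.

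**1. The plan's own figure.** G*Power's default for the within-between interaction uses λ = f²·N·m/(1−ρ), with df (k−1)(m−1) and (N−k)(m−1).
- N = 42: λ = 0.0625 × 42 × 3/0.5 = 15.75, df 2 and 80, power 0.946.
- The smallest N reaching 0.95 is 43, or 44 with equal arms.
- 42 meets 0.95 exactly if ρ is slightly above 0.5 (power 0.954 at ρ = 0.52).

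The figure is thus reproduced to within rounding. Other readings do not give it: the group main effect needs 141, and f = 0.25 entered on the ANOVA-table scale needs 126 to 128.

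**2. The conversion.** Partial eta-squared = f²/(1+f²).
- f = 0.25: 0.0625/1.0625 = 0.059.
- Partial eta-squared 0.10: f = √(0.10/0.90) = 0.333.

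**3. Whether the repeated-measures scaling rescues 0.10.** When f is scaled to the single-visit SD, the interaction's ANOVA-table effect is f²·m/[(1−ρ)(m−1)].
- At ρ = 0.5: 0.0625 × 3/(0.5 × 2) = 0.1875, so partial eta-squared is 0.1875/1.1875 = 0.16.
- It equals 0.10 only if 0.09375/(1−ρ) = 0.111, that is ρ ≈ 0.16, and then N for 95% power is about 72.

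No setting that gives 42 also gives 0.10.

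**4. Power if ANOVA partial eta-squared 0.10 is the planning effect.** λ = f²(N−2)(m−1), with f² = 0.111 and m = 3.

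| N | λ | Power |
|---|---|---|
| 42 | 8.89 | 0.748 |
| 48 | 10.22 | 0.811 |
| 73 (74 with equal arms) | 15.78 | 0.950 |

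Using N in place of N−2 in λ gives 77% at 42 and N = 72 for 95%.

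**5. What f = 0.25 means as an arm difference.** Let the arms differ by 0, d, d single-visit SDs at the three visits. Centred over time this is −2d/3, d/3, d/3, with mean square 2d²/9. Split between two arms (divide by 4), f² = d²/18.
- d = 0.25 × √18 = 1.06. The pattern 0, d, 0 gives the same.
- For a graded pattern 0, d/2, d: f² = d²/24, so d = 0.25 × √24 = 1.22.

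This step does not depend on ρ.

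**6. Power for a 0.5 single-visit SD difference** (pattern 0, d, d or 0, d, 0): f = 0.5/√18 = 0.118.

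| N | ρ | λ | Power |
|---|---|---|---|
| 42 | 0.3 | 2.50 | 26% |
| 42 | 0.5 | 3.50 | 36% |
| 42 | 0.7 | 5.83 | 55% |
| 48 | 0.5 | 4.00 | 40% |

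**7. Detectable difference at 42, by correlation.** Substituting f² = d²/18 into λ gives d² = λ(1−ρ)/7. Holding λ at 15.75 (power 0.946), d is √1.575 = 1.25 at ρ = 0.3, √1.125 = 1.06 at ρ = 0.5 and √0.675 = 0.82 at ρ = 0.7. On the separate scale of change-score SDs, a two-sample t test with 21 per arm detects 0.89 SD at 80% power and 1.14 SD at 95%.

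**The case against.** The strongest reply is that the input to the calculation was f = 0.25, that 42 follows from it, and that the parenthesis about partial eta-squared did no work. Most of this stands. The slip did not produce the 42: f = 0.333 under the same settings gives N = 25. On the plan's own definition of its effect, power is 0.946 at 42 and 0.970 at 48, so the 95% claim is essentially met on that definition. A reader might infer that the sample size was miscalculated or that the 95% claim is simply untrue. The document does not support either.

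It is also fair to say that the correlation of 0.5 and the effect-size option are inferred, and that any power quoted for 0.5 SD depends on them. That is why a range is shown and the SD is named each time.

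Two further inferences should be resisted. One is that about 1 SD is too large for a single session: the article gives no expected n-back difference or SD, so it offers no benchmark. The other is to bring in power for two time points because section 2.12 describes the time factor as before versus after or during stimulation. The calculation in section 2.5 is explicitly for three measurements, and that mismatch is a separate matter.

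What the reply does not remove is the false equivalence itself, or the fact that medium describes a different design. Neither is a detail that an article would leave to a fuller document; both are printed in the justification.

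**Conclusion.** The point holds as a wrong statement in the power justification. The failure of the direct conversion (0.059, not 0.10) needs no assumption. That no setting giving about 42 yields 0.10 rests on reading the test as the group × time interaction under G*Power's repeated-measures scaling, where the value is about 0.16. If 0.10 was truly intended, the planned sample has 75% to 81% power with three measurements, not 95%.

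The objection to the medium label rests on the same scaling and on the time pattern: 1.06 single-visit SD if the effect appears at one or both later visits, 1.22 if it is graded. The power for 0.5 SD also depends on the correlation. The consequence lies in what the trial is said to be able to detect, not in how many participants it enrols.

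**What to change.** In section 2.5, delete or correct the stated equivalence with partial eta-squared 0.10 and drop the word medium. Name the G*Power effect-size option and the assumed correlation. Then state what the fixed sample detects, with its unit and assumptions. For example:

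*With 42 completers (21 per arm), three measurements and an assumed correlation of 0.5, the group × time test has about 95% power for a between-arm difference in change of about 1.06 SD of a single measurement, present at one or both later visits; the corresponding difference is 1.25 SD at a correlation of 0.3 and 0.82 SD at 0.7.*

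If a two-sample comparison of change scores is preferred as the description, give 0.89 and 1.14 SD of the change score at 80% and 95% power, and say that these are change-score SDs.

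Enrolment stays at 48. The cost is a few sentences and a less favourable statement of power.
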